# Exclusion criteria

The exclusion criteria are set as follows: patients who (1) cannot communicate due to cognitive dysfunction, (2) cannot speak Japanese, (3) cannot make outpatient visits, and (4) are aged under 20 years.

Cognitive dysfunction may render it impossible for patients to communicate with the researcher and to operate the tablet device. We considered that the inability to speak Japanese and cognitive dysfunction would affect patient evaluation because the patients would be unable to communicate with the researcher. In addition, the inability to go to the hospital as an outpatient was considered to affect the evaluation, since the patient’s ADLs had declined, resulting in an inability for the patients to perform self-care and coping behaviors on their own.

# Methods and duration of the study

# Research design

1. Research design

This is a randomized, controlled trial conducted on two groups of patients: an intervention group using an ICT-based tele-nursing intervention program for patients with chronic respiratory failure receiving NPPV at home (in addition to usual care) and a control group receiving usual care.

1. Rationale for setting up the study design

The purpose of this study is to evaluate the effectiveness of a tele-nursing intervention program for patients with chronic respiratory failure receiving NPPV. To this end, the study design was set up as a randomized, controlled trial based on the hypothesis that the group of patients who undergo the tele-nursing intervention program (intervention group) will have fewer temporary outpatient visits (percentage and number of visits) due to acute exacerbations during the intervention period than the group of patients who receive only usual care (control group).

# Overview of the distance nursing intervention program and observations

The tele-nursing intervention program for the prevention of acute exacerbations in patients with chronic respiratory failure undergoing NPPV uses a tele-nursing system developed by the researcher based on preliminary findings and literature review, in which patients with chronic respiratory failure undergoing NPPV, according to their individual physical and mental statuses, can proactively perform self-monitoring. The nursing intervention program is aimed at preventing acute exacerbations of chronic respiratory diseases by incorporating self-management strategies, such as coping behaviors for symptoms, into the lives of patients undergoing NPPV, based on their individual physical and mental conditions. This program is conducted in collaboration with the physician in charge of the patient, as it includes information that can be utilized for the patient’s medical treatment, although it is an action outside of normal medical treatment. The program mainly consists of (1) a remote monitoring of the participant's daily physical condition, (2) health counseling on questions and problems in the participant's daily life, and (3) the provision of information on lifestyle and self-management to reduce the occurrence of respiratory symptoms. Moreover, the program has the following components: (1) data input using tablet terminals from the homes of patients with chronic respiratory failure receiving NPPV, (2) remote monitoring and health counseling from the researchers' PC terminals, (3) a database server, (4) the attending physician of the Department of Respiratory Medicine at Tohoku University Hospital, and (5) cell phone communication. Tablet terminals will be loaned by the researcher. Once a day, at a particular time, the participant uses approximately 10 min to respond to questions displayed on the tablet terminal from a list of options, and data on his/her physical condition are sent to the server. The data include vital signs, respiratory symptoms, food intake status, defecation status, medication status, physical symptoms other than respiratory symptoms, and the patient’s questions to the medical staff. After the patient enters vital signs and other measurement information into the tablet, the transmitted data are immediately monitored, and triage is performed based on the trigger points for each question item and nursing responses that have been set in advance with the physician in charge. If triggers are applicable, direct physical and mental assessment is performed by telephone or videophone according to the nursing responses that have been set, and nursing support is provided based on the Pulmonary Rehabilitation Manual [30]. If no triggers are applicable, the process is terminated by message delivery. There are 24 trigger items in total. One of the trigger items is transcutaneous oxygen saturation (SpO_2_); if the SpO_2_ is above 95%, the trigger is not applicable and no nursing support is provided. If the SpO_2_ is between 94% and 90%, the trigger is set as "alert" and the patient's condition is confirmed together with other data. If the SpO_2_ is 89% or lower, the trigger is set as "applicable"; the patient's condition is confirmed, and nursing care is provided using a videophone. The response threshold and nursing response corresponding to each question item are set individually based on the participant’s condition. As an example of the nursing response, the cause of the SpO_2_ decline is assessed based on the patient's physical and mental condition, and health counseling and information are provided via a videophone on the tablet terminal screen to enable appropriate self-management actions such as medication, NPPV application, response to shortness of breath (breathing techniques), and infection prevention actions in accordance with the cause of SpO_2_ decline. After the nursing response, the details of the response are reported to the physician in charge by phone or e-mail, and the response for the following day and beyond is discussed. If the patient is unsure about the situation after receiving nursing care via videophone, the physician in charge is promptly contacted via phone call to discuss how to handle the situation. Videophone communication with the participant is conducted at the participant’s discretion or when triggered, based on the data entered on the tablet device. The tablet terminal input time period is from 8:00 am to 12:00 pm, and the nursing response is expected to take place from 1:00 pm to 5:00 pm, once a day for approximately 30 min. If the tablet device is not input for more than 2 days, a phone call will be immediately made to the target participant to resolve the cause of the problem. The server will be set up by a company that produces this system, and Secure Sockets Layer encryption will be used for transmitted data, with access to the server limited to researchers and physicians at cooperating medical institutions. The communication technology will be the Long Term Evolution service, a cell phone communication network, under a general contract with NTT DoCoMo. We considered this service to be optimal for this study because of its robust information leakage countermeasures using proprietary security features. The tablet terminals will be loaned by the researcher and will be returned after the intervention is completed.

The web-based program in the tele-nursing system consists of a patient site and a researcher site. The tablet terminal at the patient site has (1) a screen for recording daily physical condition, (2) a screen for video calls, (3) a screen for SNS input, and (4) a screen for respiratory rehabilitation information. The researcher's site will have (1) a list of the participant's telemonitoring data and (2) a screen for inputting comments. The researcher can check the participant's daily records and output the changes over time on a summary sheet.

The intervention period will be 24 weeks, and the number of ad hoc visits and readmissions during the past 12 and 24 weeks (primary endpoints) will be examined by the researcher at enrollment, 12 weeks after enrollment, and 24 weeks after enrollment, using the electronic medical record. At enrollment and at regular outpatient visits 12 and 24 weeks after enrollment, researchers will conduct a questionnaire survey about daily life, and perform respiratory function and 6-minute walk tests. In addition, activity meters will be checked 12 and 24 weeks after enrollment to collect data on the average number of steps and patient activity. Respiratory function and 6-min walk tests at enrollment as well as 12 and 24 weeks after enrollment will be performed by the researcher using equipment purchased using the research fund, since these tests are not covered by insurance and are outside the scope of usual medical care. Since the primary endpoints of this study are the number of emergency visits and rehospitalizations due to acute exacerbations of chronic respiratory diseases, the intervention will not be stopped in the event of worsening symptoms due to acute exacerbations. If the participant dies, the intervention is terminated because the study cannot continue. If a participant requests that the intervention be continued after their participation in the program, the intervention may be offered for an extended period of time, regardless of whether the participant is in the intervention or control group.

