# Centralized evaluation system

This study does not use a centralized evaluation system.

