# Safety management responsibility system (safety management measures for personal information)

The principal investigator of the research institution will take safety control measures in handling personal information to minimize the risk of information leakage. To ensure that participant data is sent and received securely over the cell phone network, a server will be installed at a system development company that has been granted the Privacy Mark certification for data acquisition, storage, and disposal. The ICT used by NTT DoCoMo Tohoku in this program has already been used to remotely monitor the lives of older local residents and its own security system has been established; therefore, the risk of information leakage was considered low; no information provision to NTT DoCoMo was assumed. During data communication, a virtual private network connection is used, and the system is set up in such a way that data leakage or falsification by a third party is impossible. The intervention is conducted in a room where privacy is maintained (such as a graduate student's room in the Department of Cancer Nursing, Tohoku University Graduate School of Medicine), and access to the room is restricted to researchers only during data viewing, telephone calls, and videoconferencing. The details of the intervention will be promptly reported to the attending physician, who will be authorized to view the participant data, and the intervention will be conducted in collaboration with the attending physician. The obtained participant data will be handled in the graduate student room. When saving the data on the USB device, a security lock should be implemented, and the USB device should be stored in a locked cabinet.

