# Burden on research participants, anticipated risks (including possible adverse events) and benefits, a comprehensive assessment of these risks, and measures to minimize the burden and risks

# Summary of anticipated benefits and disadvantages associated with participation in the study

(1) Predicted benefits

The tele-nursing intervention program used in this study is a nursing support method that may be applicable to the participants and is expected to improve their health status after the intervention. In addition, although the evaluations (respiratory function test and 6-min walk test) are performed outside of routine medical care, researchers will prepare the equipment and perform the tests, such that there will be no financial burden on the participants. In addition, there are no special medical practice or economic benefits to be gained by the participation of the research participants in this study compared with routine medical care.

(2) Anticipated risks and disadvantages

The tele-nursing intervention program used in this study is a non-invasive intervention and thus is expected to have few intervention-related adverse events. The anticipated disadvantage of participating in this study is a delay in receiving medical attention when a patient's condition changes. Since this program is designed for patients whose general condition is stable, the tablet terminal is not equipped with a notification function in the event of a sudden change in participant condition. Therefore, in the event of a sudden change in condition, the participant must request an ambulance immediately or visit a hospital on his/her own. The participant and his/her family will be fully informed of this, and their consent will be obtained after understanding the situation. If a change in the participant's condition is evident, the attending physician or the physician in charge should be consulted immediately for appropriate measures.

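### Nothing in the protocol keeps the researcher who gave a participant tele-nursing from testing that participant at 12 and 24 weeks, so the effort-dependent and self-reported secondary endpoints are open to arm-dependent bias.

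*Protocol*

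**What the plan says.** **Who measures.** The section on the intervention program and observations states that at enrollment and at the 12- and 24-week visits "researchers will conduct a questionnaire survey about daily life, and perform respiratory function and 6-minute walk tests". It adds that the two tests "will be performed by the researcher using equipment purchased using the research fund", because they fall outside usual care. Section 15.1 repeats that "researchers will prepare the equipment and perform the tests". None of these statements distinguishes between the arms.

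**Who delivers.** The same section lists among the program components "remote monitoring and health counseling from the researchers", working from their own PC terminals. It also says: "The researcher can check the participant's daily records and output the changes over time on a summary sheet". Section 14.3 says that "access to the room is restricted to researchers only during data viewing, telephone calls, and videoconferencing".

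**What separation exists.** Under Centralized evaluation system the protocol states: "This study does not use a centralized evaluation system". Section 8.2 gives allocation to research assistants, which separates allocation from delivery but not delivery from measurement. The text available for review contains no masking of assessors.

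**Which endpoints.** The SGRQ, EQ-5D, SCAQ, respiratory function and 6-minute walk distance are all secondary. The schema in the Overview places baseline measurement before allocation. It also states the expectation that primary and secondary endpoints will improve significantly against control.

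**The concern.** Participants cannot be blinded to daily tablet entry and videophone coaching. The main protection left for outcomes that depend on effort or judgement is to keep the person who treats apart from the person who measures, and the protocol gives both tasks to one role without dividing them.

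The planned contact differs by arm. Intervention participants send data daily over a 24-week program and are counselled by videophone when a trigger applies or when they ask. For controls, the protocol describes contact with the researchers around consent and assessment. Spirometry and walk distance respond to encouragement, although the survey schedule lists both as objective items. The SCAQ concerns self-care, which is what the program coaches. A participant may also answer more favourably to someone who has been advising them.

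What is at stake is whether a difference in these secondary endpoints at 12 or 24 weeks could be read as an effect of the program.

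**Working it through.** **1. Statements side by side.**

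| Task | Role named | Place in the protocol |
|---|---|---|
| Monitoring and counselling | Researchers | Intervention program and observations; 14.3 |
| Review of daily records | The researcher | Intervention program and observations |
| Questionnaires | Researchers | Intervention program and observations |
| Spirometry, 6-minute walk | The researcher / researchers | Intervention program and observations; 15.1 |
| Allocation | Research assistants | 8.2 |

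Delivery and measurement carry the same role name in every place. Only allocation is assigned to others.

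**2. When the bias can enter.** The schema puts baseline before allocation, so nobody has yet been coached at that point. Any arm-dependent shift enters at 12 and 24 weeks and passes in full into the change from baseline.

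**3. Illustration of size.** The protocol gives no figure for assessor bias, so there is no stated value to reproduce. The inputs are:

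- 17 per arm (section 9.1).
- Two-sided 5% level (section 10.1).
- 10% dropout (section 9.2), giving 17 × 0.9 = 15.3, or about 15 per arm.
- True effect of zero.
- A spurious shift of b SD between arms. This is an **assumption**, shown as a range.

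For context on the 17: with a difference of 1.0 and an SD of 1.0, 2 × (1.960 + 0.842)² = 15.7, so 16 per arm, or 18 after 10% dropout. The t-based size is 16.7, so 17 before dropout. The stated 17 lies within that range, and the present point does not depend on it.

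Standard error of the between-arm difference, in SD units, is √(2/n):

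- n = 17: √(2/17) = 0.343, df = 32
- n = 15: √(2/15) = 0.365, df = 28

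The noncentrality is b/SE, for example 0.3/0.343 = 0.875. The chance of a significant result from the noncentral t is:

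| Assumed shift b (SD) | 17 per arm | 15 per arm |
|---|---|---|
| 0 | 5.0% | 5.0% |
| 0.1 | 5.9% | 5.8% |
| 0.2 | 8.7% | 8.3% |
| 0.3 | 13.6% | 12.5% |
| 0.5 | 29.3% | 26.2% |

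**4. Relation to the planned analysis.** Section 10.1 names paired t-tests for the secondary endpoints, not a between-arm test. The table therefore illustrates the comparison with control that the Overview expects, not a test the protocol specifies for these endpoints. Paired tests within an arm would not remove the bias, because the shift sits inside the change score.

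**The case against.** **Same role is not same person.** A reader might infer that one individual both coaches and tests each intervention participant. The documents do not show this: they name a role. The contents list a section 28.3 on the roles of the secretariat and researchers. The text of the implementation structure was not available for review, so a division of duties there cannot be excluded. This stands, and the point is limited to the absence of a separation in the text available.

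**The questionnaires may already be self-completed.** Conducting a survey need not mean interviewing. The survey schedule lists questionnaires separately from interview or medical record, and a questionnaire form is appended. This also stands. What remains unspecified is whether completion takes place away from the tele-nursing researcher.

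**Part of the bias cannot be removed.** Participants know their arm, so self-reports stay partly exposed whoever collects them. Spirometry and the walk test gain most from separation.

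**Some supporting text is weak.** The absence of centralized evaluation does not settle whether assessors are masked, and the room restriction is a privacy measure. A test script cannot be called absent either, since section 16.1 lists a procedure manual that is not shown.

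**The percentages rest on an assumed shift** and on a test not named for these endpoints. They show the consequence if such a bias exists and are no evidence that it does.

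**The primary result.** A reader might conclude that the trial's main claim is undermined. It is not on this ground: the primary hypothesis concerns temporary visits, and only secondary endpoints are affected here.

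**Conclusion.** The point holds in a limited form. As written, the protocol allows a researcher who delivered tele-nursing to a participant to administer that participant's questionnaires, spirometry and walk test at 12 and 24 weeks, and no text available for review prevents it. These secondary endpoints are therefore open to arm-dependent encouragement and response bias. Baseline is not affected, and the primary visit endpoints are outside this point.

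The size is unknown. If the shift were 0.2 to 0.5 SD with no true effect, a between-arm t-test would be significant in about 9% to 29% of trials at 17 per arm, or 8% to 26% at 15, against a nominal 5%. That range rests wholly on the assumed shift.

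The documents do not establish that one individual performs both tasks, or that the questionnaires are given by interview. The change is worth making because it is cheap and reduces an avoidable bias, not because the trial fails without it.

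**What to change.** Amend the section on the intervention program and observations for the 12- and 24-week visits:

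1. Participants complete the SGRQ, EQ-5D and SCAQ themselves and seal them before any contact with the researcher who gave their tele-nursing.
2. Spirometry and the 6-minute walk follow a fixed script of instructions and encouragement, identical in both arms.
3. Where the existing team allows, both tests are run by a researcher who did not deliver tele-nursing to that participant.

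If the trial already divides these duties, a sentence saying so in that section is enough. Outpatient nurses should not be counted on as testers: the adverse-event response section involves them in safety arrangements for the walk test but does not say that they attend or run it.

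**Cost.** Some rescheduling of existing researchers at two visits and a short script, with no added procedure and no change to sample size or analysis. Some participants will reveal their arm, and a small site may manage only the questionnaires and the script. Self-reports from unblinded participants will remain partly open to bias and should be interpreted accordingly.

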
Chronic respiratory failure is defined as respiratory insufficiency that persists for more than 1 month [21]. The most common cause of chronic respiratory failure is chronic obstructive pulmonary disease (COPD), which accounts for 45% of patients with chronic respiratory failure [22]. According to a 2008 World Health Organization report [23], COPD is expected to become the third leading cause of death by 2030, and the number of patients with chronic respiratory failure is expected to increase in the future. The White Paper on Home Respiratory Care reported that many outpatients with COPD receive home oxygen therapy (HOT) and NPPV [24], indicating the advancement of home healthcare for patients with chronic respiratory failure. In addition, non-pharmacological therapies, such as respiratory rehabilitation and patient education on daily living activities, have become the mainstay of treatment, and a common treatment strategy has been established, regardless of the causative disease [23]. According to the American Thoracic Society and European Respiratory Society, respiratory rehabilitation is "a comprehensive medical intervention based on a thorough patient assessment, followed by exercise therapy, education, and behavior modification; it also involves the improvement of the physical and psychological status of patients with chronic respiratory disease and adherence to behaviors for long-term health promotion. NPPV is defined as the use of a nasal-mouth mask interface primarily during sleep, as a form of ventilatory support therapy for chronic respiratory failure, to reduce arterial blood gas levels, dyspnea, and morning headache and fatigue. Since it does not require tracheal intubation, patients can lead their daily lives without problems such as difficulty in speaking, eating, and drinking. The introduction of NPPV in patients with chronic respiratory failure has improved the life expectancy and significantly improved the quality of life (QOL) [25] of patients. However, chronic type II respiratory failure does not only involve hypoxemia due to impaired gas exchange, but also coexists with hypercarbia due to ventilatory failure [21]. In addition, patients with chronic respiratory failure receiving NPPV experience a decreased range of activity due to respiratory symptoms and pain when wearing masks, which is a disincentive to utilizing NPPV equipment and increases the risk of carbon dioxide (CO_2_) narcosis [27]. Patients with type II respiratory failure may be perceived as living the same daily life as patients with type I respiratory failure; however, in addition to developing hypoxia, they are prone to developing hypercarbia and therefore must learn to manage their more complex physical condition. It is assumed that patients who easily increase their oxygen level to cope with dyspnea or shortness of breath during an acute exacerbation may induce a high CO_2_ state, thereby triggering CO_2_ narcosis. Acquiring the knowledge and appropriate behavior to cope with respiratory symptoms will reduce the chance of inadvertent CO_2_ narcosis. In addition, patients with chronic respiratory failure receiving NPPV have poor respiratory function reserve and exercise tolerance and thus can easily develop acute exacerbations due to the common cold [23]. This can lead to deterioration of cardiac failure and other systemic conditions, which can be immediately fatal. Patients with chronic respiratory failure have respiratory symptoms, such as cough, sputum production, and dyspnea; hence, it is difficult to notice changes in acute exacerbations, which may lead to a delay in seeking medical attention, resulting in a more serious situation. Prolonged or repeated hospitalization leads to a decline in activities of daily living (ADLs), which in turn leads to a decline in QOL [25].

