# Evaluation items and methods

# Primary endpoints

Since the purpose of this study is to verify the effectiveness of a tele-nursing intervention program for the prevention of acute exacerbations of chronic respiratory diseases, it is necessary to set the status of acute exacerbations as an evaluation item. Acute exacerbations cannot be determined simply by considering the number of temporary visits and rehospitalizations separately, and thus, the primary endpoints of this study are the statuses of temporary outpatient visits (rate and number of visits) and rehospitalizations (rate and number of hospitalizations) due to acute exacerbations in the past 12 and 24 weeks, as well as the reasons for the outpatient visits or hospitalizations at enrollment (baseline) and 12 weeks after enrollment. The data will be collected from the patients themselves at baseline, 12 weeks after enrollment, and 24 weeks after enrollment. However, if the patient's complaint is unclear, it will be collected from the patient's medical record.

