# Statistical analyses

# Statistical analysis methods

Data on basic participant characteristics will be examined for normality using the Kolmogorov-Smirnov test, and the differences between the means or medians for the data in the intervention and control groups will be compared using the *t*-test, based on the normality of the data. Fisher's exact test will be used to compare the primary endpoints of temporary outpatient visit and readmission rates between groups, and student *t*-test will be used to compare the number of temporary visits and readmissions between groups. Paired *t*-tests will be used to compare changes in secondary endpoints at baseline, 12 weeks after enrollment and intervention initiation, and 24 weeks after enrollment and intervention initiation (at the end of the intervention period). The analysis will be conducted using a personal computer with Microsoft Windows 8.1 OS installed and IBM SPSS version 21.0 statistical software, with a two-tailed significance level of 5%.

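### The primary endpoints leave out death, so a fatal exacerbation with no earlier visit or admission is either a non-event or missing, never a failure

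*Protocol*

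**What the plan says.** The Primary endpoints section explains that the trial must measure the status of acute exacerbations, and then defines this through health-care contacts only: "the primary endpoints of this study are the statuses of temporary outpatient visits (rate and number of visits) and rehospitalizations (rate and number of hospitalizations". Only contacts caused by an exacerbation count, over 12 and 24 weeks. Under Statistical analysis methods, "Fisher's exact test will be used to compare the primary endpoints of temporary outpatient visit and readmission rates between groups", and the numbers of visits and readmissions are compared by Student t-test. The section on interim analysis applies the same methods at 12 weeks and allows early termination for superiority.

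The one sentence on a participant's death stands in the overview of the intervention program: "If the participant dies, the intervention is terminated because the study cannot continue". It ends the intervention and says nothing about scoring.

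The source of the endpoint data is given in two ways. The overview of the program has the researcher examine visits and readmissions "using the electronic medical record". The Primary endpoints section says "The data will be collected from the patients themselves at baseline, 12 weeks after enrollment, and 24 weeks after enrollment", with the medical record as a fallback where the patient's account is unclear. The Survey Schedule allows interview or record.

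Two further statements bear on how plausible such a death is. On exacerbations, the Background says "This can lead to deterioration of cardiac failure and other systemic conditions, which can be immediately fatal". The section on anticipated benefits and disadvantages says "The anticipated disadvantage of participating in this study is a delay in receiving medical attention when a patient's condition changes", and adds that the tablet cannot signal a sudden change, so the participant has to seek help unaided.

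**The concern.** The stated aim is to prevent acute exacerbations, and visits and rehospitalizations stand in for them. The substitution fails for an exacerbation that kills before any contact with care: it generates neither a visit nor an admission, so it cannot be a failure on any primary endpoint.

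The protocol itself makes this case credible, since it describes fatal deterioration and names delayed attention as the anticipated disadvantage. That disadvantage is tied to the tablet program, which only the intervention arm receives during the trial. The one foreseen harm could thus act in one arm and leave no trace in the primary comparison. At stake are the two Fisher comparisons, the visit and admission counts (cut short by death), and the 12-week interim analysis, where the same scoring could feed a decision to stop for superiority.

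**Working it through.** **Inputs from the protocol.** 17 per arm and 34 in total (Basis for setting); Fisher's exact test for the rates, two-sided 5% (Statistical analysis methods). The protocol gives no mortality figure, so all event and death counts below are assumptions.

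**The planned size.** With a difference of 1.0 and a standard deviation of 1.0 visit/year, the normal approximation gives 2 × (1.960 + 0.842)² × (1.0/1.0)² = 15.7, so 16 per arm, and 16/0.9 = 17.8, so 18 after 10% dropout. The t-test version needs 17 per arm before dropout. The stated 17 is close to these, and the present point does not depend on it; 17 is used as given.

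**Weight of one participant.** 1/17 = 5.9 percentage points of an arm's event rate.

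**What happens to such a death under each data source.**
- Record-based count (overview of the program): no visit and no admission are found, so the participant is a non-event.
- Patient report (Primary endpoints): there is nobody to interview at 12 or 24 weeks, so the outcome is missing unless the record is used. The participant may then leave the denominator.

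**Effect on the test.** Assume one death from exacerbation without contact, in the intervention arm, and none in the control arm. Two-sided Fisher p-values:

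| Control | Intervention, death as non-event | Death excluded | Death as event |
|---|---|---|---|
| 10/17 (58.8%) | 3/17 (17.6%), p = 0.032 | 3/16 (18.8%), p = 0.032 | 4/17 (23.5%), p = 0.080 |
| 11/17 (64.7%) | 4/17 (23.5%), p = 0.037 | 4/16 (25.0%), p = 0.037 | 5/17 (29.4%), p = 0.084 |
| 12/17 (70.6%) | 5/17 (29.4%), p = 0.038 | 5/16 (31.3%), p = 0.038 | 6/17 (35.3%), p = 0.084 |

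Both treatments open under the present text give the same p-value to three decimals. Only counting the death changes it. In every row the intervention rate stays below the control rate.

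**More than one such death**, with control 11/17 and intervention 4/17 (non-event, excluded, event): two deaths give p = 0.037, 0.042 and 0.169; three give 0.037, 0.073 and 0.303.

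**How special these tables are.** With 17 per arm there are 153 tables in which the control arm has more events than the intervention arm, and 72 of them reach p < 0.05. Recoding one intervention non-event as an event lifts p to 0.05 or above in 13 of the 72 (18%). All three rows above belong to those 13.

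**The case against.** Five points can be made on the other side.

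- **No rule scores death as a success.** A reader might infer that the plan counts a fatal exacerbation as a good outcome. The documents do not say so. The sentence on death ends the intervention, and under patient report, or within the 10% dropout allowance, the participant would be missing rather than event-free. This stands. Exclusion nevertheless hides the death just as well, as the table shows.
- **Handling of deaths is commonly left to a statistical analysis plan.** True of missing-data rules and analysis sets. What counts as a primary event, however, is fixed here in the protocol's endpoint definition, and death is not in it.
- **Few deaths are affected.** A participant who attends or is admitted and then dies already counts in the corresponding rate, and contacts before death can be retrieved from the record. Patients are told to call an ambulance or come in, so many fatal exacerbations would leave a contact. This stands and limits the point to deaths with no earlier contact in the window. Over 24 weeks in 34 patients there may be none.
- **The direction of the result is not at risk in the examples.** A reader might infer that one death could reverse the finding. In each illustration only significance is lost, and the tables are borderline ones. Bias between arms also requires unequal numbers of such deaths, which nothing in the documents establishes. This stands.
- **Deaths are visible elsewhere.** Death meets the protocol's definition of a serious adverse event. That makes the repair easy, but it does not bring the death into the primary comparison.

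**Conclusion.** The concern holds in a limited form. The primary endpoints omit death, so a fatal acute exacerbation with no earlier temporary visit or admission in the window is either a non-event or missing, depending on which of the two stated data sources is followed. It is never a failure, although preventing exacerbations is the trial's purpose.

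The size is 5.9 percentage points of an arm's rate per such death, enough to remove significance in 13 of 72 significant tables at 17 per arm, with no reversal of direction in the examples. This rests on assumed event counts, on such deaths falling in the intervention arm only, and on full arms of 17. With no death rate in the documents, the expected number cannot be stated. The protocol should be changed, because the repair is cheap and the gap lies where the protocol itself expects harm.

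**What to change.** In section 7 (Primary endpoints) and section 10.1 (Statistical analysis methods):

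1. Count death due to acute exacerbation as an event in both Fisher comparisons, the temporary visit rate as well as the rehospitalization rate, at 12 and 24 weeks and in the interim analysis. The visit rate must be included because the primary hypothesis is about temporary visits.
2. Keep participants who die in the analysis. Take their visits and admissions up to death from the medical record, and the cause of death from the serious adverse event report. State this source the same way in section 7 and in the overview of the program.
3. Report deaths by arm beside the visit and admission counts, since the t-tests on counts do not reflect follow-up cut short by death.

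The cost is wording only; no new data are needed. The drawback is that both rates become composites, so visits, rehospitalizations and deaths should also be shown separately.
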